### Objectives

Our primary aim is to examine the feasibility of leveraging a music therapy intervention to increase hedonic capacity among individuals with anhedonia. We also aim to examine congruence across psychometric results and interview data to generate estimates of effect size and qualitative experience. In addition, we aim to identify any correspondence between these outcomes and changes in brain activity associated with reward processing during targeted fMRI tasks. This study will generate hypotheses for testing in future studies by investigating the following research questions (RQs):

RQ 1: To what extent is the music therapy intervention feasible, based on measures of participant adherence, engagement, and retention?RQ 2: Do overall changes in participant scores on psychometric measures of anhedonia from before to after the music therapy intervention correspond with patterns in descriptions of change in interviews?RQ 3: Are pre-post changes in activity across reward processing regions during fMRI tasks associated with changes in anhedonia symptoms?

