### Study Design

Given the findings from previous case studies, a sequential mixed methods study design is suitable for use in this pre-post pilot study to explore congruences between psychometric, interview, and fMRI data regarding changes in hedonic capacity among individuals with anhedonia following the music therapy intervention. Neither a strictly explanatory nor exploratory model (according to Creswell and Plano [44] definitions) is used, but the design will prioritize quantitative data from psychometric scales and seek to understand any significant differences from before to after intervention using interview data collected after intervention. This will cautiously extend case study findings of the same music therapy intervention [21,22] to determine whether psychometric outcomes are significant at the group level, as well as to explore patterns in the interview data to better understand any changes on the 2 different outcome measures—the DARS [45] and the Snaith-Hamilton Pleasure Scale (SHAPS) [46]. It would be premature to include a control condition at this stage, and similarly, the sampling of participants will be restricted to high-functioning people with anhedonia to better understand the phenomenon before extending the research to more clinical populations, such as those with schizophrenia or MDD. In addition, the study will assess the feasibility of the intervention and study procedure to inform a subsequent larger-scale study [47]. Feasibility measures will evaluate the acceptability, adherence, and practicality of delivering the intervention in adults with high cognitive function, while preliminary estimates of intervention effects and variability will be used to inform sample size calculations and the design of a future fully powered study.

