Several psychometric measures of anhedonia could be used to identify eligible participants for this study, with the DARS being most relevant because it includes a multidimensional focus on both anticipatory and consummatory pleasure that were measured in the previous case studies and appeared appropriate [21,22]. It has also demonstrated greater sensitivity to subtle differences in a German study of a similar cohort of young adults [48] and is more personalized, with participants listing chosen activities rather than having fixed items presented. By comparison, the SHAPS is more focused on consummatory pleasure [46] and has been widely validated in clinical populations (populations with schizophrenia, substance use, or depression) [49,50], which may be relevant for subsequent studies, making it useful for inclusion as a measure of change. Despite these differences, the DARS has strong convergent validity with the SHAPS in some research [51], and this may prove useful for exploring convergence with patterns from interview data, as well as correspondence with reward processing activity.

Subsequently, task-based fMRI data will be useful to explore whether activity in reward-related regions of the brain corresponds with changes in our outcomes of interest. These data will provide an estimate of effect size and identify key regions of interest to be explored in future studies.

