### Sample Size

A sample size of 13 was selected to provide adequate depth of qualitative data (interviews) while maintaining feasibility for resource-intensive fMRI data collection. This sample size is sufficient for exploratory mixed methods analysis and effect size estimation, although it is underpowered for statistical inference [53].

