### Data Analysis

Repeated-measures *t* tests will be conducted on pre-post DARS and SHAPS scores to examine directional change. Hedges *g* will be calculated to estimate effect sizes, which will inform power calculations for a future fully powered study. *P* values will be reported descriptively but not interpreted as indicators of statistical significance, given the small sample size (N=13).

fMRI data will be analyzed using individual general linear models to identify longitudinal changes associated with the intervention. For each task, blocked-design general linear model analyses will be specified at an individual participant level in Statistical Parametric Mapping version 12 (SPM12) to model specific conditions of interest. For the reward-reversal task, this will involve contrasting unexpected punishment trials with expected reward trials. For the music task, the primary contrast will compare pleasurable music with neutral music. Repeated-measures, flexible factorial designs (within-subject factors: primary contrast×time) will be used at the group level to examine longitudinal changes. These will then inform exploratory investigations of associations between these effects and symptom improvement.

Inductive thematic analysis will be used to identify patterns in descriptions of change and group similar ideas from across the interview data [58]. Labels will be selected that verifiably represent the participant quotes contained within each theme, and these will be checked by the research team as a form of peer debriefing to identify blind spots and adjusted when found to be dissimilar.

Sequential analysis will be conducted by comparing the themes from interviews to overall changes in participant scores on psychometric measures of anhedonia from preintervention to postintervention assessments to identify any correspondences. Themes will also be compared to any changes in activity across reward processing regions during reward fMRI tasks and targeted music listening evident from preintervention to postintervention assessments that correspond with patterns of congruence in the psychometric data.

Feasibility will be documented based on verbal feedback following fMRI data acquisition and in the final interview. Anything beyond individual preferences will be used to inform necessary changes to the protocol.

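### Letting the group contrast×time result guide which fMRI effects are related to symptoms can inflate the fMRI effect sizes and pass over regions that answer RQ3

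*Protocol article*

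**What the plan says.** RQ3, under Objectives, asks: "Are pre-post changes in activity across reward processing regions during fMRI tasks associated with changes in anhedonia symptoms". Data Analysis sets an order of work. Individual models are fitted first, and then "flexible factorial designs (within-subject factors: primary contrast×time) will be used at the group level to examine longitudinal changes". The next sentence reads "These will then inform exploratory investigations of associations between these effects and symptom improvement". In context, the effects to be related to symptoms are the longitudinal effects from the group model.

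Study Design gives the fMRI data a double role: "These data will provide an estimate of effect size and identify key regions of interest to be explored in future studies". The same section says more generally that "preliminary estimates of intervention effects and variability will be used to inform sample size calculations and the design of a future fully powered study". The sample is 13, chosen for qualitative depth and scanning feasibility, and described as follows: "although it is underpowered for statistical inference".

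The Background names candidate reward regions, including the nucleus accumbens, ventral striatum, insula, anterior cingulate and ventromedial prefrontal cortex. The article does not say that a set of them is fixed before the contrasts are examined.

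**The concern.** The group step and RQ3 look at different quantities. A contrast×time effect is a change in the mean. RQ3 is about spread around that mean: whether people whose activity changes more also improve more. A region that rises in improvers and falls in non-improvers can answer RQ3 while showing almost no mean change. If the group result decides what is carried forward, RQ3 could be answered in the negative because such a region was never examined.

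The second issue is double use of the data. If the same 13 people show which regions matter and also supply the effect size there, the estimate is conditional on having been large. Regions and effect sizes for later studies are a stated product of this pilot, so the bias would sit in what it is meant to deliver.

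**Working it through.** The article has no fMRI power or effect-size calculation to reproduce, so this is an illustration under stated assumptions.

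**Inputs.** n = 13, single group, pre-post (Sample Size, Study Design). The fMRI threshold, the true effect and the true correlation are not given. Assumed: selection at two-sided p<0.05, one-sided p<0.001 or two-sided p<0.001; true standardised change d = 0.2, 0.5 or 0.8; true brain-symptom correlation 0 or 0.6.

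**1. Smallest change that can pass.** d_min = t_crit(12 df)/√13, with √13 = 3.606.

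- Two-sided p<0.05: 2.179/3.606 = 0.60
- One-sided p<0.001: 3.930/3.606 = 1.09
- Two-sided p<0.001: 4.318/3.606 = 1.20

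**2. Mean observed d among regions that pass in the positive direction.** The observed t is noncentral t with 12 df and noncentrality d√13. The mean of t/√13 is taken over t > t_crit.

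| True d | Two-sided p<0.05 | One-sided p<0.001 | Two-sided p<0.001 |
|---|---|---|---|
| 0.2 | 0.79 | 1.27 | 1.38 |
| 0.5 | 0.86 | 1.30 | 1.41 |
| 0.8 | 0.99 | 1.36 | 1.46 |

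For a true d of 0.5 the inflation is 0.86/0.5 = 1.7-fold at the lenient threshold and 1.30/0.5 = 2.6-fold at one-sided p<0.001. At the strict thresholds the answer hardly depends on the truth.

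**3. What this would do to planning, if such a figure were used.** Paired design, 80% power, two-sided 5%, normal approximation: n = ((1.960 + 0.842)/d)².

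- d = 0.5: (2.802/0.5)² = 31.4, so 32 pairs
- d = 0.86: (2.802/0.86)² = 10.6, so 11 pairs
- d = 1.30: (2.802/1.30)² = 4.6, so 5 pairs

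**4. Chance that an RQ3-relevant region survives.** If the true mean change is zero, the chance of passing equals the test level whatever the correlation with symptoms: 5% at two-sided p<0.05 and 0.1% at two-sided p<0.001, both directions counted. With a true d of 0.5 it is 38% and 3%.

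**5. Effect on the correlation.** In 1,000,000 simulated samples per scenario, with regions kept on positive mean change, a true correlation of 0 gave a mean selected r of 0.00. A true correlation of 0.6 gave 0.51 to 0.57 at two-sided p<0.05 and 0.41 to 0.50 at two-sided p<0.001, across true d from 0 to 0.8. Without selection the mean was 0.58. Selection on mean change therefore pulls r down if anything.

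**6. Precision without any selection.** Fisher z at r = 0.5: 0.549 ± 1.96/√10 = 0.549 ± 0.620, which transforms back to a 95% CI of −0.07 to 0.82.

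**The case against.** The strongest objection is that no hard gate is written down. The group results are to inform exploratory work, and the article nowhere limits the associations to regions that pass a threshold. The Abstract's Methods lists associations with symptom improvement and longitudinal change side by side, and RQ3 refers to reward regions without requiring a group effect. This stands, so the point is conditional: it holds to the extent that the group result chooses the regions. The order in Data Analysis and the reference back to the group effects still make that the natural reading.

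A reader might also infer that the brain-symptom correlations are circular and inflated. The documents do not support this. That would require choosing regions on the correlation itself, which is nowhere described; selection on mean change leaves r unbiased at zero and attenuates it otherwise.

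A third objection is that the only effect size explicitly tied to power calculations is Hedges g on DARS and SHAPS, which involves no region selection. That is right. The fMRI concern rests on Study Design, which takes an fMRI effect size and the regions from one dataset and speaks generally of effect estimates informing sample size. Harm to a later sample size is possible, not stated.

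Finally, region lists and thresholds may sit in a fuller plan, and the study calls itself exploratory and underpowered. Their absence here is not the point. The exploratory label limits significance claims, but it does not remove bias from an estimate carried forward or align the group step with RQ3.

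**Conclusion.** The point holds in conditional form and is worth acting on. The stated order, together with the double use of the same 13 people, invites two errors if the group result selects regions. The fMRI time-effect sizes would be inflated: a true 0.5 would average about 0.86 to 1.30 between two-sided p<0.05 and one-sided p<0.001. Regions with opposing individual changes would pass only about 5% to 0.1% of the time between two-sided p<0.05 and two-sided p<0.001. All these figures rest on assumed thresholds and effects, and treat one region at a time. It should not be concluded that the article prescribes a hard gate or that the RQ3 correlations are inflated.

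**What to change.** Before the post-intervention contrasts are examined, fix a list of reward regions from those named in the Background; which ones is the sponsor's choice. In every listed region, whatever the group time effect:

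- take each participant's pre-post change in the primary contrast;
- estimate its association with symptom change on both SHAPS and DARS;
- report every r and every d with a 95% CI.

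Label whole-brain results as hypothesis-generating, and take no planning effect size from regions chosen on these data.

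The cost is about one paragraph of analysis plan and region extraction; no new data are needed. The Results section puts the analysis before the end of 2026, after data collection closed, so the order can still be set. The downside is that effects outside the listed regions become descriptive only. The change removes the selection bias but not the imprecision: with 13 people the intervals will stay wide, and the report should say so.

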**Methods:**

This pilot study uses a sequential mixed methods design to first identify whether there are pre-post changes in the primary outcome measures and then to identify correlations between interview data, psychometric data, and objective measures of brain structure and functioning (fMRI). Participants were 13 adults with high cognitive function who scored within the clinical range for anhedonia on the Dimensional Anhedonia Rating Scale (DARS). Participants were engaged in a 4-month music therapy intervention developed through preliminary case studies, which involved daily independent pleasure-focused music activities and regular contact with a therapeutic guide. The fMRI data acquired include resting-state fMRI and task-based functional paradigms designed to probe musical pleasure (music listening task) and reward prediction (reversal reward learning task). Data will be analyzed using individual general linear models to identify associations with symptom improvement, as well as longitudinal changes in functioning.

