### Outcomes

Feasibility will be primarily assessed in terms of participant adherence, engagement, and retention. Adherence will be evaluated by tracking participant attendance and the number and proportion of intervention sessions completed, with reasons for nonadherence recorded to determine whether these are related to the intervention or other factors. Engagement will be assessed by documenting completion of each component of the intervention, including participation in music therapy activities and any prescribed between-session practice, alongside interventionist ratings of participant engagement and proficiency where applicable. Participants will also be asked to provide brief open-ended feedback regarding their ability to engage with the intervention and any difficulties encountered. Retention will be assessed by recording the number and proportion of participants who withdraw from the study and those who complete the final assessment, with reasons for dropout documented. These measures will be used to determine whether the intervention can be delivered as intended, identify barriers to participation, and establish whether adherence and retention rates support progression to a larger definitive trial.

At baseline, participants complete an intake interview wherein demographic information including personal background and role within the university is recorded, as well as relevant information relating to participants’ general physical and mental health, experience of pleasure in daily life, any specific loss of pleasure in music, pleasure in preferred activities and lifestyle, and their historical and current relationship to music and music activity. A descriptive baseline of participants’ current level of hedonic capacity, including current experience of pleasure, enjoyment, social engagement, motivation, and decision-making capacity, is also recorded. These topics are revisited in a postintervention exit interview to capture perceived changes in pleasure experience and lifestyle associated with increased hedonic capacity; participant experience and characterization of musical pleasure through the intervention process; and participant experience of the intervention. Interview transcripts are generated for qualitative analysis. For interview questions, refer to Multimedia Appendix 1.

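### The mixed-methods integration compares themes only with fMRI changes that already agree with the scores, and never pairs a participant's interview with that participant's own score change

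*Protocol article*

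**What the plan says.** The protocol article describes the integration of interviews, scores and imaging in four places.

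- **Abstract, Methods.** The sequence is "to first identify whether there are pre-post changes in the primary outcome measures and then to identify correlations between interview data, psychometric data" and imaging measures.
- **Objectives, RQ2.** The question is whether overall score changes "correspond with patterns in descriptions of change in interviews". RQ2 concerns scores and interviews only. Brain activity belongs to RQ3.
- **Study Design.** The scores take priority, and the stated purposes include "to determine whether psychometric outcomes are significant at the group level". The interviews are then used to "seek to understand any significant differences from before to after intervention using interview data collected after intervention".
- **Data Analysis.** Inductive thematic analysis is to "group similar ideas from across the interview data". The sequential step consists of "comparing the themes from interviews to overall changes in participant scores on psychometric measures of anhedonia", looking for correspondences. Themes are then also compared with fMRI changes "evident from preintervention to postintervention assessments that correspond with patterns of congruence in the psychometric data".

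Two other statements bear on the point. Outcomes says that pre-post score comparisons will also be used to assess change in individual participants. Data Analysis plans a group-level contrast-by-time fMRI analysis followed by exploratory associations with symptom improvement, and that analysis carries no agreement filter.

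**The concern.** Congruence across data sources is a named aim. The pilot has no control group and its P values are descriptive, so agreement between sources is one of the few things that could support an observed score change. It gives that support only if the comparison could also have shown disagreement.

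Two features of Data Analysis weaken this:

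1. The last clause on fMRI selects brain changes on agreement with the psychometrics before they meet the themes. A reward-region change that runs against the scores has no place in that comparison.
2. The RQ2 comparison sets themes formed over all interviews against overall score change. A participant who describes improvement but scores worse, or the reverse, need not show up in either summary.

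At stake is how a statement such as *interviews, scores and imaging were congruent* should be read when it is used to design the next study.

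**Working it through.** The plan gives no figure for congruence, and N=13 was chosen pragmatically, so there is nothing to reproduce. The check sets out what the stated rules do when there is no true association. The input from the documents is n = 13 (Sample Size). The number of regions K, the proportion p improving on each source, and the reading of correspondence as same direction are assumptions, because the article gives none of them.

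**A. Keeping only fMRI changes that agree in direction**

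Suppose K independent regional changes, each unrelated to DARS change. Each agrees in direction with probability 0.5, so P(at least one agrees) = 1 − 0.5^K.

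| K | P(at least one region agrees) |
|---|---|
| 1 | 0.500 |
| 5 | 0.969 |
| 10 | 0.999 |
| 20 | >0.9999 |

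The size of the retained correlations follows from the null distribution of r. The mean of r among the positive values equals E|r| = Γ((n−1)/2) / (√π · Γ(n/2)). With n = 13 this is Γ(6) / (√π · Γ(6.5)) = 120 / (1.772 × 287.9) = 0.235. A simulation of 5,000 runs gave 0.234 to 0.236 for the retained regions and 0.00 over all regions. The filter alone therefore turns a true correlation of zero into an average of about 0.23 to 0.24 among the regions kept.

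**B. Comparing at group level only**

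Suppose a proportion p improves on the scores and, independently within persons, the same proportion describes improvement. Let q = P(at least 7 of 13 improve), from the binomial distribution. The two majorities agree with probability q² + (1−q)². Raw agreement within a person is p² + (1−p)².

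| p | q | Majorities agree | Raw per-person agreement | Mean kappa (simulated) |
|---|---|---|---|---|
| 0.6 | 0.771 | 0.647 | 0.52 | about 0 |
| 0.7 | 0.938 | 0.883 | 0.58 | about 0 |
| 0.8 | 0.993 | 0.986 | 0.68 | about 0 |

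For p = 0.7: 0.938² + 0.062² = 0.879 + 0.004 = 0.883.

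**C. A fixed-count example**

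Suppose 9 of 13 improve on the scores and 9 of 13 describe improvement (assumed counts). The group summaries match exactly. The same 9 people may improve on both, giving 13 concordant and 0 discordant. At the other extreme, the 4 non-improvers on one source are all different from the 4 on the other. Then 9 + 9 − 13 = 5 improve on both, none is unimproved on both, and 4 + 4 = 8 are discordant. The group comparison cannot tell 0 discordant participants from 8. A 13-row table can.

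A and B show the direction in which the rules push. They do not estimate what this study will find.

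**The case against.** The strongest reply is that this is a small exploratory study and that the restriction is narrow.

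- **The RQ3 analysis is unfiltered.** This stands. Discordant brain changes can still appear in the contrast-by-time analysis and its associations with symptom improvement. A reader might infer that only agreeing fMRI changes go forward anywhere, or that the filter distorts RQ2. The text supports neither. The clause governs only the comparison of themes with fMRI.
- **Overall change is ambiguous, and individual change is assessed.** This stands in part. Outcomes provides for individual score change, and nothing prevents the team from noticing a discordant participant. But nothing pairs that change with the person's interview or calls for discordance to be reported.
- **Coder knowledge of the scores.** A reader might infer from the scores-first sequence that themes are coded with the results known. The article does not say so, and masking may be left to the full protocol. The adjustment of labels in Data Analysis most naturally means fit to participants' quotes, and the peer check is a safeguard.
- **Interview framing.** Outcomes says the exit interview is meant "to capture perceived changes in pleasure experience and lifestyle associated with increased hedonic capacity". That might look like prompting for improvement, but baseline topics are revisited, difficulties are asked about, and the question list is in an appendix that is not shown.
- **Role of congruence in the next study.** Limitations might be read as making congruence a condition for the controlled study. It says the control group follows once it is known whether congruences exist. Either answer satisfies that wording.
- **The figures are assumed.** This stands. They illustrate the mechanism and do not measure bias in these data.

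**Conclusion.** The point holds in a limited form. Followed as written, Data Analysis selects on agreement in the theme-versus-fMRI comparison. It also leaves RQ2 as a comparison of pooled themes with overall change, which can look congruent while individuals are discordant. The first part rests on reading the fMRI clause as restrictive, which is its natural sense. The second rests on the absence of any stated link between a participant's account and that participant's scores.

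The size cannot be derived from the article. Under the assumptions shown, apparent agreement is close to certain with 5 or more independent regions, and it occurs in about 65% to 99% of cases at group level when 60% to 80% improve on each source. The consequence is bounded: the study is hypothesis-generating, the RQ3 analysis is unaffected, and biased coding is not shown. This is a cheap improvement.

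**What to change.** **Cheap improvement.** Two changes to Data Analysis:

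1. Delete the restrictive clause. State that themes will be compared with all tested reward-region changes, whether or not they agree with the psychometric results.
2. Add a participant-level joint table. Each of the 13 rows gives the change the participant describes in the interview beside that participant's DARS change and SHAPS change. Report concordant and discordant cases, and discuss the discordant ones.

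The cost is one reworded sentence and one table. Results reports that data collection has ended and analysis is due by the end of 2026, so both changes can be made without touching study conduct. The downside is a possibly less tidy congruence result.

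Optionally, state whether first-pass coding is done without sight of the score changes. An explanatory reading with the scores known could still follow, labelled as such. This is a suggestion, not the correction of a demonstrated error.
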